## Background

Laparoscopic Roux-en-Y gastric bypass (RYGB) has in recent years been the standard operation in Swedish bariatric surgery. The operation is well studied and we have a good idea of the expected result regarding weight, BMI, comorbidities, and it can be performed with a low complication rate. However, this does not mean that the surgical method is without challenges, and above all there is a small but important group of patients with prolonged morbidity after the procedure. Due to the bypassing of the duodenum and proximal jejunum, there is also a concern for long-term risk of various types of deficiency conditions.

Laparoscopic sleeve gastrectomy (SG) is a relatively recently introduced surgical method that in recent years has gained rapid and wide spread internationally and is currently the most commonly used obesity surgical technique in the United States. However, there are not results from long-term studies to the same extent as for RYGB. However, the reported data indicate good results regarding weight development and resolution of comorbidity up to a few years after the operation, although to a somewhat lesser extent compared to after RYGB. There are currently no long-term data presented for SG.

RYGB has been associated with a non-negligible risk of internal herniation with small bowel obstruction, which appears to affect at least 10% of patients operated on without closure of mesenteric defects, and despite closure a risk remains. This risk of internal herniation does not exist with SG. Another advantage of SG is that it avoids the problems with the Jejunojejunostomy (JJ), which seems to be part of the rare but difficult to treat morbidity after RYGB. There is also probably a slightly lower risk of vitamin and mineral deficiency because the duodenum and proximal jejunum are not bypassed. However, there are data that suggest that problems with gastro-oesophageal reflux may occur or worsen after SG and that continuous acid-suppressing treatment may be necessary. There are also indications that revisional surgery rates may be higher after SG, e.g. due to unsatisfactory weight development over time.

Today, therefore, there is no scientifically based unequivocal answer to which surgical method is best for the individual patient. The choice of surgical method is often based instead on local/regional guidelines and traditions, and sometimes on the patient's wishes or the surgeon's preference. There is therefore a great need for data that can provide information on how the outcome differs between operations and, in particular, if there are differences regarding outcomes in different subgroups of patients. This information is of great value to the healthcare provider as well as surgeons and patients. Internationally, there are a number of ongoing studies that compare RYGB and SG, however with a limited sample size (n=100–200) and where, as a rule, weight loss was chosen as the primary outcome variable. Existing data therefore do not allow comparisons between the surgical methods within different subgroups of patients (eg male/female, younger/middle-aged, +/- different types of comorbidity).

Scandinavian obesity surgery has a unique position and opportunity to answer the question: which of RYGB or SG should be recommended. The patient base in Sweden is relatively large with 5–6000 operations annually and with a national quality register - SOReg - with a 97.9% coverage rate. In Norway, approximately 3,000 operations are

75 carried out annually. With the help of social security numbers and data from national  
76 health registers at the National Board of Health and Welfare and other authorities, in  
77 Sweden we can plan for a complete long-term follow-up regarding factors such as health  
78 care consumption (Patient Register and Medical Register), working ability  
79 (Försäkringskassan), diabetes development (Medical Register and National Diabetes  
80 Register (NDR)) and cancer incidence (Cancerregistret). In Norway, we can use the  
81 cause of death register, cancer register, prescription register, SSB and NPR data to  
82 obtain a complete long-term follow-up.

83  
84 Bariatric surgery in Sweden and Norway is characterized by great consensus and  
85 openness between operating units. In the internationally recognized obesity surgery  
86 study SOS (Swedish Obese Subjects), basically all patients who underwent obesity  
87 surgery in Sweden over a 15-year period (n=2010) were included and followed, which  
88 has led to decisive publications that strongly position Scandinavian bariatric surgery.

89  
90 Surgically, there is also agreement regarding technical aspects of how bariatric surgery  
91 should be carried out, where in principle all surgeons perform a laparoscopic gastric  
92 bypass with antecolic antegastric technique according to the Sahlgrenska model. There  
93 is also great consensus regarding the technology for the sleeve. There is great openness  
94 in sharing results and clinical experiences, which has been facilitated to a large extent  
95 with the help of good registration in SOReg and joint complication conferences. In  
96 Norway, sleeve gastrectomy has been introduced at a rapid pace and most centers today  
97 offer both methods to their patients. The methods are largely standardized in the same  
98 way as in Sweden.

## The study

We want to compare the outcome of RYGB and SG in a large study that includes several outcome variables in addition to weight control, and with a sufficiently large number of patients to allow comparisons within different subgroups (specification see below). This is done via a national registry-based randomized controlled multicenter trial where patients are randomized to RYGB or SG. In this way, we obtain unique data that will contribute to being able to define what role SG and GBP should have in future Scandinavian and international bariatric surgery.

Follow-up of the patients will take place in the regular structure for follow-up in SOReg after 6 weeks, 1 year, 2 years, and after 5 years. In addition, via SOReg and registry studies, we want to follow the patients for the rest of their lives. Through good baseline characteristics of the patients and planned follow-up with coordination of quality registers and other national registers, we expect to be able to achieve close to 100% follow-up of the patients regarding various outcome measures.

It should be noted that the Ethics Review approved lifelong follow-up in registers, but that the first patient information states that the code key is destroyed 10 years after the end of the study. Thus, new consent may be needed to look at 15-year data and beyond, this should be investigated in good time before such a follow-up becomes relevant.

### Primary outcome measure

To evaluate whether SG has advantages compared to previous standard GBP, we want to investigate whether the surgical methods are equivalent (non-inferiority) regarding weight loss and weight stability five years after the operation, and whether SG is associated with fewer long-term complications (superiority). The primary outcome measure is thus based on a balanced assessment of long-term weight control and the frequency of serious complications.

Serious complications (Substantial Adverse Events) are defined as:

- Death caused by complication of bariatric surgery.
- Intervention in general anesthesia (Clavien-Dindo 3b and higher) for complication to bariatric surgery. Among these, gallstone interventions, hernias that were present before the primary operation and plastic surgery due to excess skin are excluded. Subgroup analysis of negative laparoscopies is planned.
- Intensive care as a result of a complication to obesity surgery  
Revision surgery (change of surgical method, reversal or significant change of original method) Revision surgery is performed according to clinical practice. The indication for revision surgery, e.g. unsatisfactory weight development or possible occurrence of GERD must be documented.
- Hospital care for an operation-related complication (apart from observation less than 1 day)
- Need for enteral (via tube to the GI tract) or parenteral total/supplemental nutrition
- Chronic abdominal pain (> 6 months) that requires regular (several times per week or daily) medication of opiates (ATC code N02A, including Tramadol and

- Codeine) and/or abdominal pain that significantly affects daily life (prevents normal work, leisure activities, etc.)
- Frequent and severe meal-related problems that affect the normal way of life for at least 3 months (eg hypoglycaemia, pain, vomiting, nausea).
  - Hypoglycemia associated with loss of consciousness/convulsions or requiring drug treatment
  - Gastro-oesophageal reflux problems that cannot be controlled with medication (including volume reflux). Barrett's esophagus (in cases where you had a preoperative normal endoscopy within 2 years before the op).
  - Clinically relevant, symptomatic deficiencies of vitamins and/or minerals.
  - Severe anemia; Hb <100 g/L in women and <110 g/L in men.
  - Other serious complication that is not predefined but after assessment by the reference group is judged to be surgery-related

Information regarding complications is collected during visits and registered in SOReg where a number of complications are listed but where there is also a field for "other". The seriousness of the complications is assessed continuously and finally after 5 years (primary endpoint). In case of doubt, the severity of the complication is determined by a reference group, which consists of 3 experienced bariatric surgeons ([name], [name], [name]).

In the calculations for long-term complications (5 years), i.e. patients who have undergone GBP and who incur some kind of serious complication (need for surgery for complication, revision surgery, serious nutritional problems, or chronic abdominal pain), it has been shown during the course of the study that the number of substantial AE (adverse events) is significantly higher than we initially expected. This has made it possible, after renewed power calculations based on new data, to reduce the number of included patients, ie. see Statistical analysis plan v 5.

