## Participating Clinics

Participating clinics in Sweden and Norway must register in SOReg.

The clinic must have a volume of at least 100 bariatric surgeries/year. To be certified as a BEST clinic, you must have performed at least 20 operations each of GBP or SG as well as having sent in a film of one type of procedure of each technique. Each clinic has a local PI who sends type-films to the trail management to verify agreement in method between participating operators and clinics. The type films are after February 2017 are verified blindly with respect to the clinic. The videos will be deleted when the review is complete.

Patients who are not included in the study are treated according to the clinic's usual treatment strategy.

Through regular joint web-based conferences, we will be able to verify consistency in assessments and surgical technique.

In addition to the usual mandatory parameters in SOReg, participating centers undertake to also register the otherwise voluntary parameters (e.g. smoking, level of

education, weight at surgery, blood pressure, quality of life) and to take the blood samples recommended in SOReg. For the health economic analysis, EQ5D-5L is used. This is filled in by the patients at baseline, as well as after 1 year, 2 years and 5 years.

A financial compensation is paid to participating clinics (currently only in Sweden) of SEK 800 per randomized patient and SEK 400 for the patient's 2- year follow-up. Our ambition is also to be able to finance five regional coordinators with the help of granted research funds to improve the follow-up rate at the 2- and 5-year examinations, or contribute in a similar way to an improved follow-up rate. The costs are initially assessed to be equivalent between the two surgical methods.

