### **Publication plan**

Planned main publications are estimated to be:

- Peri-operative results: 30-day results, mainly complications
- Two-year results: weight and adverse events
- Five-year results: weight and adverse events
- Five years: cost-effectiveness

We plan that one person from each center that contributed to the inclusion of at least 100 people will be invited to be a co-author. The aim is to publish under "On behalf of the BEST study group", and all authors are listed and credited in the work. However, for the final decision of the order of authors, the journal's guidelines must be taken into account.

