### 91 3.2 Randomization

92

93 The randomisation sequence was generated using Stata version 12.1 with a fixed block size of 10.  
94 Patients are randomized in the ratio of 1:1, stratified by the participating bariatric surgery clinics  
95 (centers).

96 The results of randomization will be provided centrally using computerized system and cannot be  
97 affected by individual operating clinics.

98 The surgeon performing the operation will be aware of group allocation at maximum one day before  
99 the actual operation. If the patient chooses, he/she will be informed the day before, or on the  
100 morning of the day of surgery, whereas those who do not wish to be informed preoperatively will be  
101 informed postoperatively about the surgical method used. For safety reasons all patients will be  
102 informed about the surgical method used. Informed consent is given before randomization by all  
103 participants.

104

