| Frequent and severe food-related problems | Affecting everyday living for at least 3 months (such as hypoglycemia, pain, vomiting, nausea) in accordance with the "BEST/ SOReg template" available on the website.                                                                    |
| Severe postprandial hypoglycemia          | Hypoglycemic episodes associated with loss of consciousness/seizures or requiring drug treatment                                                                                                                                          |
| Severe GERD                               | GERD symptoms that cannot be controlled with medication (e.g., volume reflux). Barrett's esophagus (with endoscopy performed within 2 years before surgery showing absence of Barrett).                                                   |
| Serious nutritional problems              | Need for enteral (using a feeding tube to the gastrointestinal tract) or total/supplemental parenteral nutrition                                                                                                                          |
| Chronic abdominal pain                    | Pain (>6 months) requiring regular (> 1 time/week) medication with opioids (ATC code N02A, including tramadol and codeine) and/ or abdominal pain significantly affecting daily life (prohibiting normal work, leisure activities, etc.). |
| Substantial micronutrient deficiencies    | Clinically relevant, symptomatic, vitamin and/or mineral deficiencies                                                                                                                                                                     |
| Severe anemia                             | Hemoglobin <100 g/L in women and <110 g/L in men.                                                                                                                                                                                         |
| Other serious complication                | Not pre-defined but, based on clinical data combined with national registry data, deemed to be a serious adverse event related to the surgery. If need be, these events can be assessed by a reference group.                             |

148

149 Secondary outcomes:

| Outcome                                      | Time frame                  | Explanation                                                                                                                 |

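### Judgement-based parts of the co-primary safety outcome go to the reference group only when there is doubt, no masking of outcome raters is described, and the protocol and SAP disagree on 'other' events

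*Combined protocol and SAP*

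**What the plan says.** **Outcome.** SAP version 5, section 4, analyses time to the first substantial adverse event. A patient either has an event or does not, so a single qualifying row in Table 2 is enough. Superiority of SG is tested at a two-sided 2.5% level (section 5.2).

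**Open allocation.** SAP section 3.2: "The surgeon performing the operation will be aware of group allocation at maximum one day before" the operation. Patients are told the method after surgery at the latest. SOReg, where complications are entered, also holds the operative data (protocol, Operating methods).

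**Collection and rating.** Protocol, Primary outcome measure: "Information regarding complications is collected during visits and registered in SOReg where a number of complications are listed". Then: "The seriousness of the complications is assessed continuously and finally after 5 years (primary endpoint". The rater is not named. The route to central review is: "In case of doubt, the severity of the complication is determined by a reference group, which consists of 3 experienced bariatric surgeons".

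**'Other' events.** The protocol's list of serious complications ends with: "Other serious complication that is not predefined but after assessment by the reference group is judged to be surgery-related". The corresponding row of SAP Table 2 says: "If need be, these events can be assessed by a reference group".

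**Safeguards.** Register linkage is a second source of events (SAP sections 3.4, 4 and 5.4). Food-related problems follow a template, and the pain row has an opioid criterion with an ATC code (SAP Table 2). Joint web conferences check that assessments are consistent (protocol, Participating Clinics).

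**The concern.** The rows on pain affecting daily life, food-related problems, uncontrolled reflux and clinically relevant deficiency turn on how severe a symptom is judged to be. Hospital care and 'other' events turn on whether the problem is attributed to the operation. The protocol's background links reflux to SG, and deficiency risk and jejunojejunostomy problems to bypass. It also says that the choice of method sometimes follows the surgeon's preference. A person who knows the operation may therefore grade, attribute or doubt the same complaint differently in the two arms.

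If that happens, the hazard ratio is biased directly, and a larger sample does not remove the bias. Review only of doubtful cases does not protect against it, because a confident but operation-influenced rating raises no doubt.

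**Working it through.** **1. The rules side by side**

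| Question | Protocol | SAP version 5 |
|---|---|---|
| Who rates seriousness? | Not named | Not named |
| What triggers central review? | Doubt about severity; whose doubt is not stated | Need, for 'other' events only |
| Is review of 'other' events required? | Yes, before they count | Optional |
| Are outcome raters masked? | Not described | Not described |

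The third row is a direct conflict in the most open-ended component of a co-primary outcome.

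**2. What the safeguards settle.** Registers can show admissions, ICU stays, reoperations and opioid dispensing. They do not grade symptoms, and by themselves they do not establish that an admission was due to the operation. The template covers one row. The ATC criterion covers one of two ways to meet the pain row; the other is effect on daily life. The conferences address consistency and are not described as masked.

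**3. The plan's own figure.** The SAP appendix gives 87.5% power for 25% versus 16.25% with 413 per group. A two-proportion normal approximation gives 87.6% at two-sided 5%, so the figure is reproduced at that level. At the plan's two-sided 2.5% the result is 80.8%. That gap is a separate matter; the figure is used here only to anchor the method.

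**4. False-positive rate under an assumed rating difference**

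Inputs: 1752 patients (SAP appendix), taken as 876 per arm under 1:1 allocation; common risk (25% + 16.25%)/2 = 20.625%; critical value 2.241 for two-sided 2.5%. The shifts of 1, 2 and 3 points are assumptions.

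SE = sqrt(2 × 0.20625 × 0.79375 / 876) = 0.0193

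Rejection probability = Φ(d/SE − 2.241) + Φ(−d/SE − 2.241)

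| Shift d | Patients in one arm (d × 876) | d/SE | Rejection probability |
|---|---|---|---|
| 0 | 0 | 0 | 2.5% |
| 1 point | 9 | 0.52 | 4.5% |
| 2 points | 18 | 1.03 | 11.4% |
| 3 points | 26 | 1.55 | 24.5% |

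The base rate matters. If rating lowers the SG count by 1, 2 or 3 points, the results are 5.6%, 17.0% and 39.2% from a 13% base, and 4.3%, 10.4% and 22.3% from a 25% base.

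**5. The opposite direction.** With true risks of 25% and 16.25% and 876 per arm, power is 98.9%. Overcounting SG by 2 or 4 points lowers it to 88.4% or 55.4%.

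**6. If the 35% statement is a success rule.** SAP section 4 says superiority would require more than 35% fewer patients with an event. At 20.625% the gap must exceed 0.35 × 20.625 = 7.2 points, or 0.0722 × 876 = 63 SG patients; at 25% it is 0.35 × 0.25 × 876 = 77. With a 3-point shift (20.625% versus 17.625%), the log risk ratio is −0.157 with SE sqrt(0.79375/(876 × 0.20625) + 0.82375/(876 × 0.17625)) = 0.0986. The chance that the observed ratio falls below 0.65 is Φ((−0.431 + 0.157)/0.0986) = Φ(−2.77), about 0.3%.

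**7. Review load.** Expected event patients at the appendix rates: 0.25 × 876 + 0.1625 × 876 = 219 + 142 = 361. If 20% to 40% qualify only through judgement-based rows (assumption), that is 72 to 144 cases. This is a minimum: it leaves out candidates that are rejected, and judgement-based events that precede a hard event in the same patient and so set the time to first event.

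**The case against.** The strongest reply is that much of this rests on silence and that the plan has real safeguards. Several stronger readings are tempting, and the documents do not support them.

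- **That the treating clinic rates every event and alone decides on referral.** Information is collected at visits, but neither the rater nor the person whose doubt counts is named, and the protocol already sends every 'other' event to the group.
- **That the reference group is unmasked.** The most that can be said is that no masking is described. The protocol also refers to a published method manuscript and to separate plans for each publication, which were not available here.
- **That the film review is a precedent for hiding the operation.** The protocol says: "The type films are after February 2017 are verified blindly with respect to the clinic". That masks the clinic, not the operation.
- **That bias favours SG, or that 25% is the trial's error rate.** The documents give neither the share of judgement-based events nor a direction.
- **That two-year results will influence later ratings.** The publication plan lists "Two-year results: weight and adverse events" without a date. Patients operated on at the close of inclusion (31 March 2022) reach 2 years in March 2024 and 5 years in March 2027, so overlap is possible, but an effect on ratings is not shown.

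The 35% sentence also stands as an objection if it is enforced, although it may only restate the design effect. The hazard ratio and its p-value would still be exposed. The safeguards reduce the problem; they do not make decisions on symptom severity or relatedness independent of knowledge of the operation.

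**Conclusion.** The point holds in limited form. In an open superiority comparison, the written rules allow judgement-based events to be counted without central review and without any described masking, and the protocol and SAP contradict each other on 'other' events.

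A net rating difference of 1 to 3 points (about 9 to 26 patients in one arm) would raise the false-positive rate from 2.5% to between about 4.5% and 25%. This assumes 876 per arm, a common risk of 20.6%, no true difference and no enforced 35% rule. It shows how sensitive the test is; it does not estimate actual bias, whose size and direction are unknown. This is a cheap improvement to a co-primary outcome, not evidence that ratings are biased.

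**What to change.** In the protocol's Primary outcome measure section and in SAP Table 2:

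1. Align the SAP with the protocol so that every 'other' event goes to the reference group. Table 3 of the perioperative analysis plan has the same optional wording.
2. Send every candidate event in the judgement-based rows to the existing group by default, whether it was found in SOReg or in a register. Include relatedness of hospital care where that alone decides the event. Do this at least for patients with no earlier hard event.
3. Give the group a short standard summary without the operation name and operative details, and record whether the reviewer could tell the operation.
4. Complete decisions on events up to 2 years before the group sees two-year results by arm.

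**Cost.** A short amendment and more work for a group that already exists: at least about 70 to 145 cases under the assumed 20% to 40% share. Masking will be imperfect for operation-specific problems, and nomination of symptom events will still depend partly on clinics that know the operation.
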